#### **Abstract**

Voluntary Medical Male circumcision (VMMC) is an effective strategy to reduce the risk of HIV acquisition in heterosexual men. Observational data and randomized controlled trials (RCTs) conducted in Africa suggest that the procedure reduces the risk of HIV acquisition by 50-76% in heterosexual males. VMMC has also been shown to reduce the incidence of other sexually transmitted infections (STI), including herpes simplex virus type 2 (HSV-2) and human papilloma virus (HPV) in men, and Chlamydia, trichomonas vaginalis (TV), bacterial vaginosis (BV) and HPV in their female partners.

The results of the RCT's are generating increased demand for safe and affordable MC services in areas of moderate-to-high HIV prevalence where the MC rates are low. Latin America is a region where circumcision of males is uncommon. In the Dominican Republic (DR), which is the focus of this study, a 2007 nationwide household survey found that only 13.7% of men between the ages of 15-59 were circumcised.

AIDS is the leading cause of death in the Caribbean basin among adults aged 15-44 years. There are approximately 240,000 people currently living with the disease, most of them residing in the Dominican Republic (DR) and Haiti. The prevalence of HIV infection in the DR is approximately 0.8% nationwide but it is higher in selected high-risk populations, such as among people living in the "bateyes", the small towns surrounding sugar cane plantations, where the prevalence is 3.2%. In pregnant women seeking prenatal care at the main hospital in the Altagracia province HIV seroprevalence is 4.5 %. One of the areas of highest prevalence (1.2%) in the country is Region V of health, which includes the provinces of La Altagracia, El Seibo, Hato Mayor, La Romana and San Pedro de Macorís. Prevalence is also higher in the urban slums of the capital city, Santo Domingo.

The public health impact of introducing MC as a strategy to prevent HIV/STI transmission in areas of high HIV/STI prevalence and low MC rates can be significant. In addition to decreasing the rates of HIV and other STI, the intervention could indirectly help decrease the rates of HPV associated cervical cancer. The study proposed here is to develop, implement, monitor and evaluate pilot MC services in selected sites to assess the acceptability, uptake, safety and demand for these services, and to use these data to develop, in collaboration with the Dominican Ministry of Health (MoH), a proposal to the National Institute of Mental Health (NIMH) for support of operations research concerning the safety, uptake, and efficacy of MC interventions in the DR.

### **a) Specific Aims:**

Based on the results of numerous observational studies and the three RCTs the World Health Organization (WHO) and the Joint United Nations Programme on HIV/AIDS (UNAIDS) have endorsed VMMC as a biomedical intervention for HIV prevention. As such, countries with a high prevalence of HIV in the population are encouraged to examine the feasibility of offering MC services as part of the portfolio of HIV prevention strategies at a national level. The specific aims for this project are:

- 1) To develop culturally appropriate education materials about the benefits of VMMC for clients attending pilot healthcare centers.
- 2) To train a core group of providers on proper surgical and counseling techniques to provide comprehensive VMMC services.
- 3) To determine the acceptability, uptake and demand for MC services in key areas of high HIV prevalence.  
H1: The acceptability and uptake among high risk men will be around 60%.
- 4) To assess the safety and adverse events of performing circumcision in resource constrained settings.  
H2: VMMC will result in a complication rate of less than 2%.
- 5) To assess sexual risk behaviors, perceptions of sexual function and sexual pleasure in men before and after VMMC. H3: there will be no differences in risk behaviors, sexual function and pleasure after VMMC
- 6) Estimate point prevalence of most common STI in a subset of circumcised men and preserve a small sample of blood to test future scientific hypothesis and/or newer testing techniques as they become available.
- 7) To build collaborations with the MoH and other partners in the DR and at UIC to develop a proposal to NIMH for operational research in the context of larger scale MC service provision.

### **b) Background and significance:**

#### **b.1. Male Circumcision to Prevent HIV Transmission**

Male circumcision is perhaps one of the oldest surgical procedures performed on humans. The millenary practice of removing the male foreskin has cultural, religious and medical dimensions that have been widely studied. Around the world, the procedure is

mostly performed for religious reasons in persons of the Jewish and Muslim faiths. Medical indications for MC include phimosis, paraphimosis and balanitis, among others. Early evidence of a relationship between MC and HIV infection came from a number of smaller, mostly observational studies, done in Africa. These historical data were validated with the completion of three large RCTs in South Africa, Kenya and Uganda, which have shown an overall decrease of 50-76% in the risk of acquiring HIV infection in circumcised males when compared to controls.

The pathogenesis of the initial infection at the level of the foreskin involves tissue macrophages, cell receptors and a moist, poorly keratinized inner prepuce. The first cellular target of the HIV virion on the human genitalia are the tissue dendritic cells in the lamina propria of the submucosa. These cells express surface CD4 receptors and CCR5 co-receptors for which HIV has high affinity. In intact human skin, the dendritic cells are shielded from the outer environment by the relatively thick layer of keratin covering the surface of the epithelia. Tissue studies of the human foreskin have shown that the inner lining of the prepuce, exposed during a penile erection, has a thin keratin layer that is very susceptible to microscopic abrasions and can expose the tissue macrophages making them vulnerable to infection by HIV.

#### b.2. MC for STI prevention:

MC is an effective strategy to decrease the risk of infection with HIV and other STI in heterosexual males. A beneficial effect has also been observed in decreasing the risk of STI in females. The RCTs confirmed that VMMC decreases herpes simplex virus type 2 (HSV-2) acquisition by 29%, and HPV prevalence by 34% in men. Among female partners of circumcised men, bacterial vaginosis was reduced by 40%, and trichomonas vaginalis infection was reduced by 48%. Genital ulcer disease was also reduced among males and their female partners by approximately half.

#### b.3. HIV in the Caribbean and the Dominican Republic

The significant decrease in the rate of HIV acquisition observed among circumcised males who participated in the African RCT is generating an increased demand for safe and affordable VMMC services in areas of high HIV prevalence where the procedure is not routinely performed. Latin America is one of such areas where routine circumcision of males is uncommon. In the Dominican Republic, only 13.7% of men between the ages of 15-59 years are circumcised. The Caribbean is the region of the world with the highest HIV prevalence outside of sub-Saharan Africa (1.0%). Approximately 240,000 individuals are currently living with the disease. Among the Caribbean countries, the Dominican Republic and Haiti report the highest prevalence in the region. According to data from a recent In the DR, the prevalence of HIV infection is 0.8% nationwide, however, the numbers are higher in selected populations and in certain geographic locations.

The Dominican healthcare system is administratively divided in 9 regions, which include the country's 31 provinces. Region 0 of health includes the National District and the

provinces of Santo Domingo and Monte Plata. The city of Santo Domingo is the capital and financial center of the DR. It has an estimated population of 2.7 million people spread in an area of about 1,400 KM. 90% of the population lives in an urban setting in this province. The overall prevalence of HIV is around 0.7 % in the entire region but is higher in vulnerable groups such as commercial sex workers (CSW) (3.3%), Men who Have Sex with Men (MSM) (5.9%) and drug users (7.1%).

Regions V and VII report the highest prevalence of HIV in the country, 1.2 % and 1.5% respectively. Specific populations within these provinces have rates of HIV considerably higher than the national average. For instance, prevalence is 3.2% in the bateyes, the small communities surrounding sugar cane plantations, where a mixed population of Dominicans and Haitian migrant workers cohabitate. Our team has conducted preliminary studies in the Altagracia Province, part of Region V, since it reports the highest province-specific HIV rates and the lowest circumcision rates in the country. A survey of pregnant women seeking prenatal care at the main hospital in the province found an HIV seroprevalence of 4.5 %. The prevalence of HIV is 5.2% in CSW, 7.6% in MSM and 8.5 % among drug users.

### **c) Preliminary studies:**

The parent study for this project is a RCT of VMMC to reduce HIV incidence in Kisumu, Kenya whose principal investigator is [name], a co-investigator in the current proposal. The main objective of that trial was to assess the effectiveness of VMMC in reducing HIV incidence in young, sexually active men. The protective effect found in an intent-to-treat analysis was 53% and in an as treated analysis adjusting for cross-overs and men found to be HIV seropositive at baseline estimated the protective effect to be 60%. Adverse events related to the surgical procedure were few, just 1.5%. Behavioral disinhibition (risk compensation) on the part of circumcised men was small and not significant.

Drs. [name] and [name] conducted a feasibility study of healthcare facilities in the Altagracia province in the Dominican Republic during June and July of 2007. A total of 37 healthcare facilities were surveyed. The study found that most facilities lacked appropriate equipment to perform surgical procedures and only four (11%) had a surgical theater. 43 healthcare workers, the majority of them physicians (91%), were interviewed for the study. Only 23 % of the personnel had experience performing MC and a significant number of providers (76%) believed they needed comprehensive training in the procedure prior to starting a MC program. Quantitative and qualitative studies to assess the acceptability of MC among men, women and providers in the Altagracia Province were conducted in 2008. In these studies, 73% of men thought that MC improved hygiene and approximately one third knew that it reduces the risk of penile cancer or STI. Only a small percentage (21%) knew that MC helps prevent HIV infection. When first asked, 29% of participants reported that they would be willing to be circumcised if the procedure was offered to them. However, after an educational session detailing the benefits of the procedure for HIV and STI prevention, the acceptability increased to 67%. Such increment was also observed in previous studies

done in Botswana and Thailand where acceptability increased from 61 % to 81% and from 14% to 66%, respectively, after a similar information session. In multivariate analysis, the strongest predictors of men's acceptability of circumcision, before the information session, were Haitian nationality (OR=1.86, 95% CI 1.01-3.41), thinking that circumcision improves hygiene (OR=2.78, 95% CI 1.29-6.0) and not believing that having a circumcision decreases sexual pleasure (OR=2.18, 95% CI 1.20-3.94). These results have been published in the Public Library of Science-ONE and presented at the International AIDS meetings in 2007 and 2009 in Mexico and South Africa.

We also conducted 13 focus group discussions (FGD), 6 with women and 7 with men, each consisting of 6-10 participants (mean=7.9, SD=1.3). One additional FGD was conducted with six physicians, two males and four females, working in rural clinics around the province. Findings of this qualitative study showed that a significant number of participants might be willing to be circumcised, or agree with circumcision for their partners, to improve hygiene, prevent diseases and treat medical conditions, such as phimosis, which can result in pain during intercourse. These results are consistent with our quantitative study on men's acceptability of MC. Perhaps one of the most important findings of the FGD was the enthusiastic endorsement of MC by women, a fact that has potential implications for the successful implementation of a circumcision program in the country (manuscript accepted for publication to AIDS Care.)

Overall, our preliminary data suggest that men are willing to be circumcised provided they receive information about the benefits of the procedure. Before recommending the introduction of VMMC services as part of a comprehensive package of HIV and other STI prevention strategies, these findings need to be confirmed by studying the uptake of VMMC among sexually active men in selected clinics that serve clients in high prevalence areas. In addition, there is need to identify potential barriers to offering MC services in high risk communities prior to proposing to implement a large-scale intervention. In order to properly address these concerns, we will conduct a pilot study that will provide the necessary preliminary data to design a proposal to the NIMH to conduct operational research around a large-scale implementation project.

#### **d) Experimental design and methods**

##### **d.1. Pilot study design**

The study will be conducted at two sites: the STI clinic at Instituto Dermatologico and Cirugia de Piel (IDCP) in Santo Domingo and the Clínica de Familia in La Romana, Dominican Republic. These sites have been selected on the basis of: 1) high numbers of male clients at risk for HIV and STI infection in communities served by the clinics; 2) high level of acceptability of MC among men in the communities served by the clinics (bateyes of Altagracia); 3) the availability of service providers willing to be trained; 4) the availability of equipment; and 5) the availability of infrastructure, including a minor surgical theater, sterilization facilities and HIV voluntary counseling and testing (VCT) and STI management.

### Specific aim #1:

During the first phase of the study, culturally appropriate educational material will be created in Spanish by the principal investigator and local collaborators. Focus Group Discussions (FGD) and in-depth interviews will be conducted with members of the community to learn the educational needs of the community and to assess their opinions on how to best deliver the information on MC that will be contained in the educational materials.

#### *FGD and in-depth interviews*

#### *Recruitment of participants*

We plan to conduct the FGD in the communities served by the Instituto Dermatologico and the Clinica de Familia, the two main study sites. The plan is to assemble groups of 6-12 participants from the population living in these communities. Community leaders, health promoters, teachers and primary care physicians will be asked to help identify and invite volunteers from their respective communities to participate in the study. There will be no difference in the recruitment process for men and women. They will be recruited from the same venues (schools, clubs, community centers). Participants will be invited to participate by research personnel with the help of local leaders. These local leaders may be of both genders and will help recruit participants from either gender. The focus groups will be gender-specific. The moderator will explain the purpose of the study to participants. Verbal consent will be obtained from all participants and an information sheet outlining the objectives of the study, their privacy and confidentiality rights and our contact information will be distributed. The document will highlight the voluntary nature of the subject's participation and their right to leave the discussion at anytime if they so desire. The study meets the definition of "minimal risk", therefore, we are requesting a waiver of written consent. We believe this will further preserve the confidentiality of the participants.

The goal is to conduct no more than 15 FGD. Participants in the FGD will be divided by gender. We plan to recruit approximately the same number of men and women for the FGD.

In addition to the FGD, several in-depth individual interviews may be conducted using the same guide than in the FGD.

#### *Eligibility criteria for FGD and interviews*

##### **Inclusion criteria:**

- 1) Men and women between the ages of 18 and 40.

##### **Exclusion criteria:**

- 1) Individuals with speech or hearing impairment.
- 2) Children less than 18 years of age.

### *Collecting, Processing and Analyzing the data obtained from FGD and interviews*

A script will be followed to conduct the FGD. The discussions will be stimulated by using a list of carefully crafted questions on the subject of MC. These questions are designed to obtain information on the following aspects relevant to our investigation:

- 1) Perception of the population about the frequency of MC in community men.
- 2) Opinions on the best way to educate men in the community about the benefits of circumcision
- 3) Opinions about the content of the educational materials educational and how information should be delivered
- 4) Where should these educational material be posted or distributed to capture the most number of men
- 5) Opinions on the best venue to organize educational sessions featuring a circumcised man that would be available to answer question from men in the community about his satisfaction with his circumcision
- 6) Perceptions about who would be a good person to educate men about the benefits of circumcision in the community
- 7) Opinions on the best way to involve women in the community in a campaign to recruit men for circumcision

The moderator and a research assistant (RA) will lead the discussions. All FGD will be audiotaped and detailed notes will be taken. The content of the recordings will be transcribed shortly after the end of the meeting. The PI ,a native Spanish speaker, will be responsible for translating the recordings from Spanish to English. The English-version transcripts will be coded using the program ATLAS.ti vers. 5.2 based on template of topical categories drawn from questions and issues covered in the discussion guides and from themes emerging from the discussions themselves.

The interviews will be conducted by one of the co-investigators. Verbal consent will be obtained and a document containing information about the study will be provided to the participants.

All data obtained during this study, including recordings and notes will be de-identified. The names of the participants will not be recorded to protect their confidentiality.

### *Data Management*

All notes, audio recordings and study material obtained during the FGD and interviews will be kept in a locked filing cabinet in an office at the Instituto Dermatologico, Dominican Republic and in the PI's office at the UIC campus upon the investigator's return to Chicago. All data will be de-identified to preserve confidentiality. Names will not be recorded. Verbal informed consent will be sought; there will be no signed consent forms to identify individuals. The participants have the right to review the audio recordings. If a participant requests to listen to the recordings, one of the co-investigators will schedule an appointment for the subject to come to the research site and, in an unoccupied office, will playback the recording for him/her and answer all the questions that the subject may have. If the participant wishes to erase part or all of his/her responses, it will be done on the spot, in his/her presence, using the digital recorder.

The data obtained during these FGD and interviews will inform the design of the educational materials. Once created, these materials will be tested for clarity and appropriateness of language by soliciting input from community health promoters and peer advocates working at the IDCP. Once it is determined that the educational materials are suitable to distribute to clients, we will submit to the Institutional Review Board for approval. Once approved, pamphlets and posters will be printed and distributed at the site clinics and the surrounding communities

#### Specific aim #2:

During the second phase, selected providers will be trained. This will include counselors in HIV counseling and testing, and medical doctors by an experienced urologist on the appropriate technique for VMMC using the “Manual for Male Circumcision Under Local Anesthesia” published by WHO, UNAIDS. Supervision and evaluation of trainees will be conducted following the protocol used during the parent RCT.

#### Specific aim #3

##### *Subject recruitment*

Study subjects will be recruited in a variety of ways. In Santo Domingo, fliers will be posted in bars and night clubs frequented by men at high risk for HIV/STI acquisition. A group of volunteer commercial sex workers working on an HIV vaccine trial will be asked to refer their clients for the study. Men seeking care for STI at the clinic will also be invited to participate. In La Romana, men attending the Clínica de Familia will be invited to participate. In addition, a group of outreach workers will visit the “bateyes”, the communities surrounding sugar cane fields where migrant laborers live, to educate men about MC and invite them to participate in the study. Subjects will be compensated for transport.

The inclusion criteria for the study will be:

- 1) Uncircumcised men;
- 2) Aged 18-40 years;

Exclusion criteria include:

- 1) Foreskin covering less than half of the glans;
- 2) Bleeding disorders;
- 3) Keloid formation;
- 4) Other conditions that might unduly increase the risks of elective surgery.

Men between 18-40 years will be provided with information about the study and will be invited to participate. If they express an interest in participating, informed consent will be obtained. The participant will go over the consent form with the counselor, who will

assess his level of understanding and answer any questions. If there are no temporary or permanent excluding conditions, the participant will be asked to give informed consent for enrollment in the study (appendix A). Men who elect to be circumcised will be fully informed about the benefits and risks of the procedure, as well as the surgical method to be used. After the informed consent is signed, a "Locator Information Form" (form 1) containing confidential data such as subject's name and address will be completed. Only selected research staff will have access to this information, which will be filed separate from the rest of the study forms. A de-identified "demographic information form and behavioral questionnaire" (form 2) will be completed next.

Testing for HIV infection will be carried out using a rapid test. The test kits to be used are the synthetic peptide test, Determine HIV 1/2, and the recombinant antigen test Unigold HIV 1/2 Recombinant. Results are provided to the clients, with appropriate counseling, at the same visit. Participants are taught to observe, read and interpret the tests for themselves in the company of the counselor. Men with positive results will be informed of their HIV status and will be followed-up at the study clinic and referred for a confirmatory HIV-ELISA and, if confirmed, for HIV treatment.

10 ml of blood and a urine sample will be collected at the one-week post circumcision visit. Blood will be centrifuged and two aliquots of 2 ml each will be obtained. One aliquot will be used for all study tests and the other will be preserved for future testing as outlined below and on section d.3. Serologic testing for HSV-2, hepatitis B surface antigen (HBV), and hepatitis C antibody (HCV) will be performed using an ELISA test. A serum Rapid Plasma Reagin test (RPR) will be performed to test for syphilis. Chlamydia and gonorrhea testing will be performed in urine using a Polymerase Chain Reaction (PCR) assay.

All participants who test positive for Chlamydia, syphilis and gonorrhea will be offered treatment free of charge. Participants who test positive for HSV-2 and have active genital lesions will be offered treatment free of charge. Those who test positive but have no active lesions will be counseled on safe sex practices and the risk of transmission to their partners as there is no recommended treatment for asymptomatic individuals infected with HSV-2. HIV, HBV, and HCV positive participants will be referred for evaluation and treatment at Clinica de la Familia in La Romana as these are chronic diseases that require long term treatment usually covered under government programs. If a participant is found to have a treatable STD and he does not return to the site, he will be called by the study investigators using the phone number provided by the participant at enrolment to ensure treatment is provided.

An aliquot of the patient's serum (2 mls) will be preserved for future testing at the University of Illinois. As long as the investigators hold personal identifiable information, participants will be informed of the results of any future testing performed on their blood and will be offered treatment free of charge and referrals as outlined above. Section d.3 provides a complete description of how these samples will be managed, preserved and transported. Urine will not be preserved for future testing.

If there is a temporary, medically curable condition present, such that it would be advisable to defer potential surgery, then the participant will be treated and asked to return for re-evaluation for study eligibility when he is cured. Men found to have an STD or to be HIV-positive will be referred for immediate care. Once enrollment is completed, participants will be given an appointment for the surgery.

Circumcision will be performed soon after informed consent, preferably within a few days. All surgeries will be done under local anesthesia in a clinic by trained clinicians, using the standardized forceps-guided method described by Krieger and colleagues and contained in the WHO MC manual. Circumcised men will be counseled to refrain from sex for six weeks post-surgery and counseled about risk of HIV infection through open wounds during the healing process. They will be checked for complications and asked about their sexual activity seven days after the procedure. Men without complications will be followed six months after surgery with behavioral risk assessment, HIV testing and counseling. Men may come to the study sites for unscheduled visits at any time during the 6 month follow-up. All men will be counseled at enrollment and all follow-up visits to reduce their risk for HIV infection by consistent condom use and, where applicable, reductions in numbers of sex partners. Counselling on condom use and sexual risk reduction will be provided by trained, experienced, native-speaking counsellors.

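### Aim 6 promises STI point prevalence, but RPR alone and hepatitis C antibody alone measure test reactivity, not current syphilis or hepatitis C infection

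*Protocol*

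**What the plan says.** Protocol, section a), aim 6, is to "Estimate point prevalence of most common STI in a subset of circumcised men". It does not name the infections or say what counts as a case.

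The assays are in the Subject recruitment text under Specific aim #3. For syphilis: "A serum Rapid Plasma Reagin test (RPR) will be performed to test for syphilis". For the viral infections: "Serologic testing for HSV-2, hepatitis B surface antigen (HBV), and hepatitis C antibody (HCV) will be performed using an ELISA test". Chlamydia and gonorrhea are tested by PCR in urine.

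The same section then says what happens after a positive result. "All participants who test positive for Chlamydia, syphilis and gonorrhea will be offered treatment free of charge", and "HIV, HBV, and HCV positive participants will be referred for evaluation and treatment". A confirmatory test is named only for HIV, where men with a positive rapid test are "referred for a confirmatory HIV-ELISA and, if confirmed, for HIV treatment". On the serum itself, "One aliquot will be used for all study tests and the other will be preserved for future testing".

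Section d.2 has analysis paragraphs for aims 1 to 5 and none for aim 6, so nothing there qualifies the reading. A separate analysis plan may exist but is not at hand.

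**The concern.** The protocol fixes both what is to be estimated and the assays that will estimate it, and for two infections they do not match.

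- **Syphilis.** RPR is a non-treponemal test. A reactive result can come from syphilis, from other causes, or from disease already treated.
- **Hepatitis C.** Antibody shows past or current infection and does not tell them apart.

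The text nevertheless refers to men as positive for syphilis or for HCV on these results alone. A reader of the eventual report would take the percentages as the share of men currently infected. What is at stake is the meaning of two descriptive figures. Uptake, safety and satisfaction are not affected.

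**Working it through.** **Inputs.** The protocol gives no sensitivity, specificity or expected prevalence for syphilis or hepatitis C, and no size for the aim 6 subset, so there is no stated figure to reproduce. All accuracy values below are assumptions, shown over ranges. The one number from the protocol is the planned total of 500 men (Study length and estimated sample size).

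**RPR.** With true prevalence p, sensitivity Se and specificity Sp:

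apparent prevalence = p × Se + (1 − p) × (1 − Sp)

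This exceeds p only while p is below the break-even value (1 − Sp) / [(1 − Se) + (1 − Sp)].

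Example at p = 1%, Se = 0.90:
- Sp = 0.97: 0.0090 + 0.0297 = 3.87%, and 0.0297/0.0387 = 77% of positives are false.
- Sp = 0.99: 0.0090 + 0.0099 = 1.89%, and 0.0099/0.0189 = 52% of positives are false.

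| Se | Sp | True 1% reads | True 5% reads | True 10% reads | Break-even |
|---|---|---|---|---|---|
| 0.90 | 0.97 | 3.87% | 7.35% | 11.7% | 23.1% |
| 0.90 | 0.99 | 1.89% | 5.45% | 9.9% | 9.1% |
| 0.75 | 0.97 | 3.72% | 6.60% | 10.2% | 10.7% |
| 0.75 | 0.99 | 1.74% | 4.70% | 8.4% | 3.8% |

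The bias is upward in every row at a true 1%. At a true 5% it has reversed in the last row, and at 10% in two of the four. At Se 0.90 and Sp 0.995 a true 5% reads 0.0450 + 0.00475 = 4.98%, which is essentially unbiased.

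For scale, the 95% half-width at 1% with all 500 men is 1.96 × √(0.01 × 0.99/500) = 0.87 percentage points. The bias at a true 1% in the two Se 0.90 rows is 0.89 to 2.87 points. A smaller subset would have a wider interval and the same bias.

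**Hepatitis C antibody.** Let s be the true antibody prevalence and f the share of antibody-positive men with current infection. Assume every currently infected man has antibody, so current infection is f × s.

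- With a perfect antibody test, the reported figure divided by current infection is 1/f: 1.11 at f = 0.90, 1.33 at f = 0.75 and 1.67 at f = 0.60. No assumption about test error is involved.
- With Se 0.98, s = 1% and f = 0.75 (current infection 0.75%):
  - Sp 0.98 gives 0.0098 + 0.0198 = 2.96%, or 3.95 times current infection.
  - Sp 0.999 gives 0.0098 + 0.00099 = 1.08%, or 1.44 times.
- Against seroprevalence itself, that last case is only 1.08 times the truth. Labelled as seropositivity, the figure would be close to right.

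For hepatitis C the error is therefore upward whenever Se is at least f. For RPR the direction depends on values that the documents do not give.

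**The case against.** Four stronger readings are tempting, and the documents do not support them.

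- **That the protocol defines a case as one positive screening test.** No counting rule is written. The language about testing positive sits in sentences on treatment offers and referral. Case labels can properly be left to an analysis plan.
- **That HIV is held to a higher analytic standard.** The HIV-ELISA is part of a referral for care and is not said to feed any estimate. Men positive for HCV are also referred for evaluation, again with no statement that the result comes back. There is no double standard in the analysis.
- **That prevalence will be overstated by a known factor.** Varying specificity alone at a fixed sensitivity of 90% gives an error that is always upward for true prevalence of 1-5%. Lower sensitivity can reverse it for RPR. Recruitment includes men seeking STI care and clients of sex workers, so syphilis need not be rare.
- **That these figures drive the later proposal.** The Abstract ties that proposal to acceptability, uptake, safety and demand. The objectives listed under Outcomes do not include STI prevalence.

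It can also be argued that point prevalence fixes only a time, so that seroreactivity at one visit has a point prevalence too. That is true, and it is why relabelling is enough. The second serum aliquot leaves later confirmatory work possible, but none is specified.

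What stands is the mismatch. An analysis plan can relabel a result, but it cannot supply a treponemal or HCV confirmatory result that the study does not plan to collect.

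**Conclusion.** The point holds as a minor one. The listed assays can estimate the prevalence of RPR reactivity and of anti-HCV seropositivity, but not of current syphilis or hepatitis C infection. This rests on general properties of the two tests and on the absence of any confirmatory result planned to return to the study.

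The size is conditional. If infection is uncommon the error is upward: a true 1% reads as 1.9-3.9% at assumed sensitivity 90% and specificity 97-99%. For RPR it is near zero or reversed at lower sensitivity or higher prevalence. For hepatitis C a gap remains even with a perfect antibody test, unless all antibody-positive men are currently infected. Severity is minor because aim 6 is descriptive, uses a convenience sample and lies outside the objectives under Outcomes.

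**What to change.** In section a), aim 6, and in the testing text under Specific aim #3, state that the reported quantities are the prevalence of RPR reactivity (with titre, if recorded) and of anti-HCV seropositivity (past or current). Do not present them as prevalence of syphilis or hepatitis C infection, and carry the same labels into the tables.

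Use a treponemal or HCV confirmatory result only where routine care already provides one, and say for how many men it was available.

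A sensitivity calculation for test error is optional. If done, it should vary both sensitivity and specificity over stated ranges, separately for each assay. With assumed accuracy it illustrates the uncertainty and does not correct the estimate.

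The cost is a few lines of wording, with no new test and no change to who is offered treatment or referral. The downside is that aim 6 can claim less.
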